## 6. Health-related quality of life and utility score assessments

### A. The refined Chinese version of the Scoliosis Research Society-22 (SRS-22r) questionnaire

The SRS-22r is a 22-item quality of life questionnaire for patients with spinal deformity. It comprises of 5 scales measuring function/activity, pain, self-image/appearance, mental health, and satisfaction with management. The investigators have already translated and validated the Chinese version of the questionnaire.[26] The SRS-22r has been routinely administered to all patients with scoliosis seen at DKCH through a web-enabled system. Moreover, multiple data-points should be available, as patients are required to fill in a questionnaire on every visit to the clinic.

### B. The EuroQol-5-dimension (EQ-5D) utility score

The EQ-5D comprises of 5 questions that provides the health utility input of QALYs for cost-utility of interventions. This measure has grown popularity and has been used for health-related quality of life and utility score assessment. EQ-5D scores are valid, reliable and sensitive for utility assessment in AIS patients. We will utilize the EQ-5D-5L for this study.

### C. EuroQol-visual analogue scale (EQ-VAS)

EQ-VAS ranges from 1 to 100, which represents the patient's own perception of his/her own health status on the day of clinical visit.

Summary table of assessments can be seen in Table 1.

**Table 1. Summary Table of assessments**

| Type of parameters                       | Study Parameters                                                                                                                                                                                                                                       |
|-------------------------------------------------|---------------------------------------------------------------------------------------------------------------------------------------------------------------------------------------------------------------------------------------------------------------|
| Socio-demographics                              | Date of birth, gender, ethnicity, school grade
number of siblings/family history of scoliosis                                                                                                                                                              |
| Maturity parameters                             | Clinical
Standing and sitting height, arm span, date of menarche
Radiological
Risser sign, distal radius and ulna (DRU) classification, Risser staging                                                                                               |
| Scoliosis specific parameters                   | Coronal Cobb angle
Truncal balance (truncal shift, C7-central sacral vertical line deviation)
Curve type and number of curves, apex location, apical trunk rotation
Sagittal vertical axis (SVA)
L1-S1 lumbar lordosis
T5-12 thoracic kyphosis |
| Mode of treatment                               | Duration of brace treatment
Complications of bracing                                                                                                                                                                                                       |
| Brace compliance and routine measures           | Compliance (hours) by thermal sensor                                                                                                                                                                                                                          |
| Health-related quality of life (HRQoL) measures | Refined Scoliosis Research Society-22 (SRS-22r) questionnaire
EuroQol-5 dimension (EQ-5D) utility score
EuroQol-visual analogue scale (EQ-VAS).                                                                                                         |
| Safety assessment                               | Adverse event                                                                                                                                                                                                                                                 |

## 7. BLINDED OUTCOME ASSESSMENT BY INDEPENDENT INVESTIGATORS

All scoliosis specific parameters will be evaluated by two independent investigators separately. These are radiographs which will be anonymized during assessment, and scoliometer measurements done by a designated nurse who is not involved in this study. Investigators will be blinded to the study treatment throughout the study period.

All statistical analyses will be performed using SPSS Statistics v. 28.0. (Armonk, NY, IBM Corp). Further details of statistical method and analysis will be described in a statistical analysis plan.

## **8. SAFETY ASSESSMENT**

All adverse events (AE) will be collected in this study. The description of AE, start date and end date, severity, relationship to the study protocol and outcome of the event, will be recorded. Any AE encountered will be minimal and are isolated to complications of brace-wear for the gradual weaning group. These include abrasions and bruising.

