For brace weaning, AIS patients can only rely on the surgeon’s decision rather than evidence-based guidelines. This may be a **slow weaning process**, whereby the duration of brace wear is slowly reduced or changed to night-use only, or may be a **rapid immediate removal** of the brace. The main rationale for a slow gradual weaning process over a period of at least 6 months is to allow the spine to adapt to an environment without loading by the brace while maintaining the corrective posture. We postulate that by this method, the curve magnitude measured by the Cobb angle and the overall truncal balance and posture may be maintained even after brace removal. The resulting curve magnitude is the commonly used outcome measure of treatment as it has bearing on the likelihood of curve deterioration and surgery. However, truncal balance may be a larger concern for patients due to its larger impact on overall cosmesis. Whether this theory of gradual weaning benefits holds true is unknown but is supported by our knowledge of the spine’s viscoelastic properties. The viscoelasticity of spinal structures including the ligaments, joint capsules and intervertebral discs allows deformation changes while loading and unloading the spine.[23] A lag-time response of spinal soft tissues to these changes have been demonstrated. Despite our limited knowledge on the effects of gradual weaning on the spine, deterioration in Cobb angle and truncal balance parameters may lead to worse cosmesis and quality of life, and possible need for surgery. Hence, **lack of an optimal brace weaning protocol is a significant**

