## **6. STUDY ASSESSMENTS**

All subjects will undergo weight, standing and sitting height, and arm span measurements, HRQOL and utility measurements, and whole spine standing posteroanterior (PA) and lateral radiographs at each clinic visit. The refined Scoliosis Research Society 22-item (SRS-22r) questionnaire and the EuroQoL 5-Dimension 5-Level (EQ5D) questionnaire will thus be provided at every visit for HRQOL and utility assessment. For all patients undergoing bracing, an orthotist assessment is also performed at each clinic visit for any brace modification and education. Further details regarding the measurements assessed are listed in the following pages.

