### 4. Mode of treatment

Data to be retrieved include the duration of brace treatment, as well as the corresponding start and end dates. Any previous complications from bracing including curve deterioration, abrasions and bruising will be recorded.

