## **Supplementary 2 Statistical Plan**

### **TITLE: A RANDOMIZED CONTROLLED TRIAL COMPARING GRADUAL AND IMMEDIATE BRACE WEANING FOR CLINICAL MANAGEMENT OF ADOLESCENT IDIOPATHIC SCOLIOSIS PATIENTS**

#### **DATA PROCESSING AND ANALYSIS**

##### **1. SAMPLE SIZE CALCULATION**

The sample size of this clinical trial will be determined based on an independent sample *t*-test to detect a difference between the two groups (immediate and gradual bracing weaning) for the changes in Cobb angle. According to a previous study [1], the average increase in Cobb angle at 1 year after brace weaning was 3.5 degrees. Curve progression is observed in 43.5% of patients. At 2 years, the curve progression rate was 46.5% with an average increase of major curve Cobb angle of 5.1 degrees. Based on this result, we consider a difference of 2 degrees between the changes in Cobb angle as clinically relevant, with an equivalence margin of 0.4. Assuming a standard deviation of 6 degrees for the Cobb angle change, a sample of 128 per group is required to detect the difference of the statistical test with 80% power at a 0.05 level of significance. Accounting for 20% overall attrition rate at 1 year follow-up, we will recruit 308 AIS patients (154 in each group) for this prospective study.

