##### **2. STUDY OUTCOMES**

Primary outcome was the change in major curve Cobb angle from baseline to 6-month, 12-month, and 24-month follow-up. Curve progression was examined as  $>5^\circ$  increase of major Cobb angle between follow-up time points and baseline. Secondary outcomes were the change in truncal balance in truncal shift and listing (C7-central sacral vertebral line deviation) from baseline to 6-month, 12-month and 24-month follow-up.

Secondary outcomes also included the refined Scoliosis Research Society 22-item (SRS-22r) questionnaire total score, the EuroQol-5-dimension (EQ-5D) utility score and EuroQol-visual analogue scale (EQ-VAS) at all post-weaning time points.

All study outcome measures were studied at baseline (the time of weaning), post-weaning 6, 12 and 24 months.

Body weight, standing and sitting body height, arm span, and HRQoL measures were measured, and curve type (i.e. thoracic, thoracolumbar/ lumbar) and coronal Cobb angle were assessed from whole spine standing posteroanterior and lateral radiographs taken simultaneously at each visit as per clinical routine. Skeletal maturity was routinely determined at the time of weaning using Risser staging, distal radius and ulna (DRU) classification and Sanders staging. In addition to Cobb angle and truncanl balance, other radiological parameters including T1 tilt, shoulder height, sagittal vertical axis (SVA), thoracic kyphosis (T5-12) and lumbar lordosis (L1-S1) were measured by two assessors independently. An intra-class correlation coefficient (ICC) with 95% confidence interval will be used to estimate the inter-assessor reliability.

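### The safety section prejudges adverse events as minimal and confined to the gradual arm, and renewed bracing and spinal surgery after weaning have no defined place in the results

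*Supplement*

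**What the plan says.** Final protocol, section 8 (Safety Assessment), opens with an unrestricted rule: "All adverse events (AE) will be collected in this study". For each event it asks for a description, dates, severity, relationship and outcome. It then adds: "Any AE encountered will be minimal and are isolated to complications of brace-wear for the gradual weaning group". The only examples follow: "These include abrasions and bruising". No possible event is named for immediate removal. Table 1 lists adverse events without further definition.

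The Introduction describes what loss of correction can lead to: "deterioration in Cobb angle and truncal balance parameters may lead to worse cosmesis and quality of life, and possible need for surgery".

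The SAP, under Study Outcomes, measures deterioration in everyone: "Primary outcome was the change in major curve Cobb angle from baseline to 6-month, 12-month, and 24-month follow-up". It defines progression as a rise of more than 5 degrees in the major curve, and it lists truncal balance and quality of life as secondary outcomes. Under Primary Analysis, a patient belongs to the per-protocol population only if there was no treatment in follow-up after weaning. Under Subgroup Analyses, the number and percentage with progression at 24 months are specified in the per-protocol population. A chi-square test of progression, non-progression and rebound by weaning protocol is also given there, with no population named. No part of the SAP summarises adverse events.

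**The concern.** How severe adverse events are, what causes them and in which arm they fall are things that a trial should find out. Section 8 asks staff to judge severity and relationship for each event, and then tells them the answer. Treatment is known to patients and clinicians, so the sentence can steer both what is asked and how it is graded: skin events in the gradual arm are expected, and nothing is expected after immediate removal.

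The second problem concerns events that are neither a radiographic measurement nor a skin complaint. A patient who returns to a brace or has spinal surgery after weaning has had an outcome that families and clinicians would want counted by arm. The Introduction itself mentions possible surgery. Yet the nearest the SAP comes to such events is a reason to leave the per-protocol population. The protocol's Potential Benefits section hopes that the results will support a universal weaning protocol, and that use needs a plain count of these events by randomised arm.

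**Working it through.** The point is mainly textual, so the relevant places are set side by side first.

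| Item | Measured in both arms? | Named outcome? | Named adverse event? | Summary by arm in the SAP? |
|---|---|---|---|---|
| Cobb change | Yes, at 6, 12 and 24 months | Primary | No | Yes, intention-to-treat and per-protocol |
| Progression over 5 degrees | Yes, from the same radiographs | Yes | No | Chi-square, population not named; 24-month count specified in per-protocol |
| Truncal balance | Yes | Secondary | No | Yes |
| Skin abrasion, bruising | Collect-all rule | No | Yes, gradual arm only | No |
| Renewed bracing after weaning | Collect-all rule only | No | No | No |
| Spinal surgery after weaning | Collect-all rule only | No | No | No |

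**Step 1: section 8 against itself.** The collect-all rule has no limit by arm or type. The sentence after it limits expected events in severity, cause and arm. Both cannot guide a site.

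**Step 2: where a re-treated patient goes.** The SAP does not define the post-weaning treatment that excludes a patient from the per-protocol population. I assume that it includes renewed bracing and surgery. Such a patient then leaves the 24-month progression count. The patient stays in the intention-to-treat comparison of mean Cobb change if a measurement exists; no imputation is done.

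**Step 3: direction and size of the effect on the count.** Let an arm have N patients, x of them with progression, and let r of those x be re-treated and excluded. The reported proportion is (x − r)/(N − r) instead of x/N. The difference is

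(x − r)/(N − r) − x/N = −r(N − x) / [N(N − r)],

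which is negative whenever r > 0 and x < N. The count therefore understates progression in an arm whose progressors are re-treated, and the comparison shifts if r differs between arms. A re-treated patient without progression moves the percentage the other way, since x/(N − r) > x/N.

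For scale, take the SAP's 2-year progression rate of 46.5%, which comes from a previous study and is not specific to either arm:

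- N = 154: x = 0.465 × 154 = 71.6, about 72. With r = 1 the shift is 82/(154 × 153) = 0.0035, or 0.35 percentage points.
- N = 0.8 × 154 = 123.2, about 123, applying the SAP's 20% attrition for 1 year: x = 0.465 × 123 = 57.2, about 57. With r = 1 the shift is 66/(123 × 122) = 0.0044, or 0.44 percentage points.

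The documents give no value for r, so the total effect cannot be computed.

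**Step 4: what the progression rate does not show.** At 1 year the SAP states: "Curve progression is observed in 43.5% of patients". That is 0.435 × 154 = 67 patients per arm, or 0.435 × 123 = 53.5, about 54, after attrition. These patients are captured by the progression outcome, so the figure shows how common progression may be and is not a number of lost events.

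**The case against.** The best defence is that the disputed sentence is only an expectation. The collect-all rule comes first and covers both arms, so a site that follows it would log surgery after immediate removal. Severity and relationship are already to be recorded for each event. The main harm, loss of curve control, is the primary endpoint, and the radiographs are anonymised and read by two investigators. Whether an efficacy endpoint is also logged as an adverse event is a matter of convention.

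Much of this stands, and it rules out several stronger inferences that a reader might draw:

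- *That deterioration after brace removal goes uncounted.* It does not. Cobb change and truncal balance are compared between arms under intention-to-treat, and progression has its own test.
- *That the safety comparison is one-sided by construction.* The collection rule is not limited to one arm, and the SAP specifies no safety comparison that could be one-sided. The wording invites uneven reporting; it does not impose it.
- *That the protocol already classes curve deterioration as a trial adverse event.* The text under Mode of treatment reads: "Any previous complications from bracing including curve deterioration, abrasions and bruising will be recorded". That is bracing history, not follow-up after weaning.
- *That extra orthotist contact proves unequal detection.* The protocol says: "For all patients undergoing bracing, an orthotist assessment is also performed at each clinic visit". Its stated purposes are brace modification and education, with sensor scanning in the gradual group. More notice of skin events is plausible but is not documented. Brace-related skin events in the arm that wears a brace are also a real treatment difference.

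The defence leaves three things unanswered: the contradiction within section 8, the absence of any defined place for renewed bracing and surgery, and the lack of a harms summary by arm.

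**Conclusion.** The point holds in limited form. Section 8 prejudges the severity, cause and arm of adverse events immediately after a rule that leaves these to be recorded event by event, and the open-label design makes that a reporting risk. Renewed bracing and spinal surgery after weaning have no named place as outcome or adverse event. They can take a patient out of the population in which the 24-month progression count is specified, and the SAP has no table of harms.

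The primary comparison of mean Cobb change is untouched. The likely effect on the progression percentage is small for each patient, and its total is unknown because no re-treatment rate is given. The conclusion rests on reading post-weaning treatment in the per-protocol criteria as including renewed bracing and surgery, and on taking the count as specified in the per-protocol population only. If the chi-square test is meant for all randomised patients, the concern about progression shrinks, but the gap for surgery and renewed bracing remains. The change is worth making because it is specific, cheap and reduces bias.

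**What to change.** 1. **Protocol, section 8.** Delete the quoted sentence, or neutralise it so that no severity, cause or arm is assumed. Severity and relationship are then judged for each event, as the same section already asks.
2. **Data collection.** Put the same adverse-event questions to both arms at 6, 12 and 24 months, and record any renewed bracing and any spinal surgery.
3. **SAP.** Add one table by randomised arm, with all randomised patients as the denominator, showing adverse events (brace-related skin events on a separate line, since exposure differs by arm), renewed bracing, spinal surgery, and progression of more than 5 degrees. Show the number without a radiograph at each visit, so that missing data are visible.
4. **SAP, Subgroup Analyses.** Keep the per-protocol progression count as a supplement to this table, and name the population for the chi-square test.

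Progression can stay an efficacy outcome and need not also be logged as an adverse event. The cost is a slightly longer form and one extra table, within the visits already planned. Treatment after weaning must in any case be known to apply the per-protocol criteria.

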## **9. ETHICS AND REGULATION**

The study will be conducted in accordance with the protocol, ICH GCP E6 (R2), ethical principles that have their origin in the Declaration of Helsinki and all applicable regulations. All serious violation of the above-mentioned standards/regulations must be reported by principal investigator to Independent Ethics Committee (IEC)/Institutional Review Board (IRB), and local regulatory authority when applicable. A serious violation is a breach of the conditions and principles of ICH GCP E6 (R2), study protocol and applicable regulations, which is likely to affect patient protection and data integrity of the study.

## **11. INFORMED CONSENT FORM**

The Informed Consent Form (ICF) used in the study must be reviewed and approved by the local IEC/IRB. Prior to any study-related screening procedures being performed on the patients, the Investigator or his/her designees should explain all aspects of the study to the patients and answer all their questions about this study.

The Investigator should provide the patient ample time and opportunity to inquire about details of the study and to decide whether or not to participate in the trial. If the patient voluntarily agrees to participate in the study, the written ICF should be signed and personally dated by the patient. The Investigator who conducts the informed consent discussion should also personally sign and date on the ICF.

A copy of the signed ICF will be given to the patient and the original will be placed

in the Investigator's File. The Investigator should document on the source document the date of obtaining the signed consent and that the patient received a signed copy.

## **12. DATA SAFETY AND MONITORING**

Principal Investigator shall protect the confidentiality of patients. Personal data is defined as any information or data that relates to an identified or identifiable patients or different pieces of information, which collect together can lead to the identification of a patient. Personal data includes but not limited to patient's medical records and laboratory results.

By obtaining patient's written consent, the Investigator has the patient's permission and shall permit the regulatory authorities, IRB/IEC representatives to get direct access to patient's personal data for data verification purposes.

Study data should not contain any patient's identification. All persons involved in the study are bound by this confidentiality clause. PI may only be disclosed the study data to third-party collaborator(s) as authorised by the ICF signed by the patients.

## **13. POTENTIAL BENEFITS**

Scoliosis is a lateral curvature of the spine, affecting every population worldwide. It is the most common spinal deformity that affects children and its most common form is AIS. Curve progression occurs with growth and thus timely intervention with bracing is important to control the deformity. However, prolonged bracing may lead to osteoporosis, poor muscle endurance and reduced spine mobility. Brace weaning is initiated when patients are skeletally mature. However, current brace weaning protocols are not standardized and are usually clinician dependent. Some clinicians may suggest a gradual brace weaning protocol in hope of the spine viscoelastic properties to allow maintenance of in-brace curve characteristics while some may just terminate brace treatment completely without any weaning process. Decisions are thus variable and not based on any evidence.

By determining the best brace weaning protocol associated with optimum outcomes

of maintaining Cobb angle and truncal balance, we can provide our patients with evidence-based treatment decisions that produce the greatest benefit. There are increasing demands for high-quality healthcare in including designing evidence-based management protocols, especially for the commonest pediatric spinal deformity that is AIS. There is potential for our results to support a standardized universal brace weaning protocol. We can provide good evidence-based care for tens of thousands of AIS children around the world. The results are impactful not only local but also on a global scale.

